#### 4.2. Exclusion Criteria

Any potential subject who meets any of the following criteria will be excluded from participating in the study.

1. Subject has been previously exposed to anti-HCV treatment, including any approved or investigational DAA therapy.
2. Subject has chronic liver disease of a non-HCV etiology (including but not limited to hemochromatosis, Wilson's disease,  $\alpha$ 1-antitrypsin deficiency, cholangitis, drug- or alcohol-related liver disease, primary biliary cirrhosis).  
Note: Subjects with Gilbert's disease will be allowed to participate provided they satisfy criteria outlined in exclusion criterion 8.
3. Subject is infected with hepatitis B virus (hepatitis B surface antigen [HBsAg] positive) or human immunodeficiency virus (HIV-1 or HIV-2) (HIV-1 or HIV-2 antibody test positive at screening).
4. Subject is infected with non-genotype 1 or non-genotype 4 HCV.
5. Subject has advanced liver disease equivalent to Metavir status F3-F4 (bridging fibrosis

or cirrhosis).

6. Subject has current or past history of clinical hepatic decompensation (e.g., ascites, variceal hemorrhage, hepatic encephalopathy, hepatorenal syndrome, or hepatopulmonary syndrome).
7. Subject has contraindications to the use of PegIFN $\alpha$ -2a or RBV per local prescribing information:
  - Major uncontrolled depressive illness.
  - Organ transplant (other than cornea or hair transplant or skin graft).
  - Severe concurrent medical disease including but not limited to severe hypertension, significant coronary heart disease requiring therapy, poorly controlled diabetes, untreated thyroid disease, chronic obstructive pulmonary disease, severe retinopathy or clinically relevant ophthalmological disorder, severe infections (bacterial, viral, fungal, including acute tuberculosis and active schistosomiasis), or hemoglobinopathies (thalassemia major or sickle-cell anemia).
  - Autoimmune hepatitis or other autoimmune conditions (except thyroid disease) known to be exacerbated by PegIFN $\alpha$ -2a and RBV.
  - Subject has evidence of severe retinopathy or clinically relevant ophthalmological disorder.
  - Subject has any other clinically significant disease that in the opinion of the investigator would be exacerbated by the known effects of PegIFN $\alpha$ -2a and RBV.

Note: This is a non-exhaustive list. For details, refer to the manufacturer's prescribing information or contact the sponsor. Baseline fundoscopic pathology which would require routine follow up on PegIFN $\alpha$ -2a and RBV therapy is considered exclusionary.

8. Subject has any of the following laboratory abnormalities:
  - Platelet count < lower limit of laboratory normal range (LLN);
  - Absolute neutrophil count (ANC) < 1500 cells/mm^3 (subject of black African [Sub-Saharan African] descent: < 1000 cells/mm^3);
  - Hemoglobin < 12 g/dL for women and < 13 g/dL for men;
  - Creatinine > 1.5 mg/dL;
  - ALT and/or AST > 10 x upper limit of laboratory normal range (ULN);
  - Total serum bilirubin > 2 x ULN;

Note: Subjects with total serum bilirubin > 2 x ULN are allowed in case of elevated indirect bilirubin due to Gilbert's disease and direct serum bilirubin below ULN.

  - Alpha-fetoprotein (AFP) > 50 ng/mL;

- Thyroid-stimulating hormone (TSH):
    - $< 1$  LLN or  $> 1.5 \times$  ULN, or
    - $\geq 1$  and  $\leq 1.5 \times$  ULN if free thyroxine ( $T_4$ ) or free triiodothyronine ( $T_3$ ) are outside of normal range;
  - Antinuclear antibody (ANA)  $> 1:160$ .
9. Subject has a history of clinically significant renal, cardiac, vascular, pulmonary, gastrointestinal, endocrine, neurologic, hematologic, rheumatologic, psychiatric, or metabolic disturbances or any other major medical disorder that may interfere with the subject's treatment, assessment or compliance with the protocol.
10. Subject has a history of malignancy within 5 years before screening (exceptions are squamous and non-invasive basal cell carcinomas of the skin and carcinoma in situ of the cervix, or malignancy that in the opinion of the investigator, with concurrence with the sponsor's medical monitor, is considered cured with minimal risk of recurrence). Subjects under evaluation for malignancy are not eligible.
11. Subject has known allergies, hypersensitivity, or intolerance to TMC435, PegIFN $\alpha$ -2a or RBV or its excipients (refer to IB or the respective SmPCs).
12. Subject has taken any disallowed therapies as noted in Section 8, Prestudy and Concomitant Therapy before the planned first dose of study drug.
13. Subject is a woman who is pregnant, or breast-feeding, or planning to become pregnant while enrolled in this study or within 6 months after the last dose of RBV or a man who plans to father a child while enrolled in this study or within 6 months after the last dose of RBV (or longer when dictated by local regulations), or has a pregnant female partner.
14. Subject has a history of drug or alcohol abuse that in the investigator's opinion would compromise the subject's safety and/or compliance with the study procedures.
- Note: Urine will be tested at screening to check the current use of amphetamines, cocaine, opioids, benzodiazepines, cannabinoids and barbiturates. Subjects with a positive drug test may be included at the investigator's discretion. Evidence of the investigator's assessment with regard to the subject's safety and compliance must be in place prior to the start of treatment.
15. Subject has any condition for which, in the opinion of the investigator, participation would not be in the best interest of the subject (e.g., compromise the well-being) or that could prevent, limit, or confound the protocol-specified assessments. Vulnerable subjects (e.g., imprisoned subjects) should be excluded.
16. Subject is an employee of the investigator or study site, with direct involvement in the proposed study or other studies under the direction of that investigator or study site, as

well as family members of the employees or the investigator.

17. Subject with genotype 4 HCV infection has currently active schistosomiasis (i.e., positive Ag blood test or positive rectal snip). Subjects with a history of schistosomiasis may be included at the discretion of the Investigator.
18. Subject is infected with genotype 1 **and** genotype 4 HCV.

**NOTE:** Investigators should ensure that all study enrollment criteria have been met at screening, prior to declaring a subject eligible to start treatment. If a subject's status changes (including laboratory results or receipt of additional medical records) after screening but before the first dose of study drug is given such that they no longer meet all eligibility criteria, they should be excluded from participation in the study. Section 17.4, Source Documentation, describes the required documentation to support meeting the enrollment criteria.

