Dose adjustments of TMC435 are not allowed. **If TMC435 is discontinued because a subject meets a virologic stopping rule, it must not be restarted.** If PegIFN $\alpha$ -2a is discontinued for tolerability or toxicity issues or if > 2 consecutive weekly injections are missed, RBV and TMC435 must be discontinued. If RBV is interrupted for more than 14 consecutive days, TMC435 must be discontinued; PegIFN $\alpha$ -2a may be continued at the investigator's discretion. Any additional interruption of RBV or PegIFN $\alpha$ -2a should be discussed with the sponsor on a case-by-case basis.

Temporary interruption of TMC435 during the treatment period will be allowed in the event of suspected toxicity, as long as the temporary interruption is associated with and can be linked to an AE or SAE (permanent discontinuation of one or more study medications may be required, see Section 9.5.7 and Section 10.2). One single treatment interruption for toxicity reasons of TMC435 will be allowed with a maximum duration of 4 days. Treatment with TMC435 should be reinstituted as soon as the AE is stabilized. Reinstitution of TMC435 treatment after interruption for longer than 4 days or after repeated interruption is generally disallowed unless approval by the sponsor has been obtained after discussion on a case-to-case basis.

All modifications, interruptions, or discontinuations of TMC435, PegIFN $\alpha$ -2a, and RBV will be recorded in the eCRF.

Study-site personnel will instruct subjects on how to store study drug for at-home use as indicated for this protocol.

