### **9.1.2. Screening Phase**

The screening period will last maximum 6 weeks. Legitimate delays in starting treatment may be approved by the sponsor through upfront written communication/motivation by the site and written approval by the sponsor.

Screening assessments as outlined in the Time and Events Schedule can be done during the screening period and need not necessarily be done at the same moment. When the cap for enrolment has been reached for a specific IL28B genotype, stepwise screening can be performed: after signing of the ICF, IL28B screening can be done first. If the lab results show that the subject has another IL28B genotype than the one for which the enrolment cap was reached, further screening assessments can be undertaken. This way subjects who have an IL28B genotype for which maximum enrollment has been reached do not need to undergo all screening assessments.

Upon confirmation of all eligibility parameters, including availability of all central laboratory parameters, the baseline visit can take place. The locally approved product information of PegIFN $\alpha$ -2a (Pegasys) and RBV (Copegus) should be taken into account to determine eligibility (see also Section 4.1, Inclusion Criteria and Section 4.2, Exclusion Criteria).

Except the tests specified in the Section 4.2, Exclusion Criteria, if the results of other clinical laboratory tests are outside the normal reference ranges, the subject may be included only if the investigator judges the abnormalities or deviations from normal to be not clinically significant or to be appropriate and reasonable for the population under study. This determination must be recorded in the subject's source documents and initialed by the investigator.

Host *IL28B* genotyping is mandated for all subjects who participate. This will be specified on the ICF: subjects who consent to participate in the study also consent to *IL28B* genotyping.

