a The homeostasis model assessment for insulin resistance (HOMA IR) index will be derived from insulin and glucose (fasted) test results at baseline, Week 4, Week 12, Week 24, Week 36, and Week 48 (as applicable).

b Safety sampling will also include a TSH test at screening, and thereafter every 12 weeks after the start of study treatment until the end of PegIFN $\alpha$ -2a and RBV treatment. In case of clinically significant abnormal TSH levels, reflex testing for free T3 and free T4 will be performed.

c The biochemistry sample taken at screening will include testing for glycosylated hemoglobin (HbA1c) and ANA.

The central laboratory will estimate the creatinine clearance (CLcr) according to the formula derived from the Modification of Diet in Renal Diseases (MDRD) study.

A midstream urine sample must be provided for local urinalysis by dipstick. If there are clinically relevant abnormalities in the investigator's opinion, further urinalysis should be done locally (e.g., sediment analysis including RBC, WBC, casts). Any clinically relevant findings from this local analysis should be reported as an AE.

- Urinalysis

- Dipstick**

- specific gravity
  - pH
  - glucose
  - protein
  - blood
  - ketones
  - bilirubin
  - urobilinogen
  - nitrite
  - leukocyte esterase

- Serum (at screening, all female subjects) and urine (at other time points, female subjects of childbearing potential only) pregnancy testing will be performed. Extra pregnancy test kits will be given if more than 4 weeks between two consecutive study visits to perform a pregnancy test at home. The results of the urine pregnancy test should be recorded in the eCRF and in the subject's medical records.
- At screening, serology for HIV-1 and HIV-2 antibody, hepatitis A immunoglobulin M (IgM), HBsAg, and anti-HCV antibody will be performed.
- At the screening visit, an additional midstream urine sample must be provided for a urine drug screen. The drug screening involves analysis for amphetamines, benzodiazepines, cocaine, cannabinoids, barbiturates and opioids.
- At screening a schistosomiasis antibody test will be performed. If the schistosomiasis antibody test is positive, a schistosomiasis antigen blood test or rectal snip should be performed.
- At the screening visit, AFP will be tested for all subjects. FSH will be tested for female subjects who are postmenopausal for less than 2 years.

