#### **9.5.7.6. Toxicity Management for Specific Adverse Events Considered to be at Least Possibly Related to PegIFN $\alpha$ -2a and Ribavirin**

Note: the information below does not imply that the following AEs are caused by PegIFN $\alpha$ -2a or RBV therapy alone, they may also be due to TMC435.

Management of AEs associated with the use of PegIFN $\alpha$ -2a and RBV will be at the discretion of the investigator, taking into account generally accepted medical standards for patient monitoring and management, and the investigator's clinical judgment and clinical practice. General guidance is provided in the sections below. In addition, the manufacturer's prescribing information for PegIFN $\alpha$ -2a (Pegasys) and RBV (Copegus) should be consulted.

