**Table 8: Guidelines for Subjects Developing Anemia**

| Laboratory values                                             | Reduce only RBV dose to 600 mg/day a if hemoglobin level is                             | Discontinue RBV b if hemoglobin level is |
|---------------------------------------------------------------|----------------------------------------------------------------------------------------------------|-----------------------------------------------------|
| Hemoglobin in subjects with no cardiac disease                | < 10 g/dL                                                                                          | < 8.5 g/dL                                          |
| Hemoglobin in subjects with history of stable cardiac disease | $\geq 2$ g/dL decrease in hemoglobin during any 4-week treatment period (permanent dose reduction) | < 12 g/dL despite 4 weeks at reduced dose           |

a One 200 mg tablet in the morning and two 200 mg tablets in the evening.

b If the abnormality is reversed, RBV may be restarted at 600 mg daily and increased further to 800 mg daily at the discretion of the treating physician. However, returning to higher doses is not recommended. If RBV has to be discontinued, TMC435 must be discontinued as well; PegIFN $\alpha$ -2a may be continued at the investigator's discretion.

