### 9.5.7.6.4. Renal Complications

Renal safety will be monitored by evaluating serum creatinine levels, estimate CLCr (according to the formula derived from the MDRD study and serum chemistry results. The investigator should closely monitor for disturbances in serum creatinine. If renal complications develop, subjects must be treated as clinically appropriate. The study medication may be continued if the renal complication is considered not to be related to the study medication in the opinion of the investigator. RBV should be discontinued in subjects with creatinine > 2mg/dL or CLCr < 50 mL/min.

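### Exclusion 8 sets no CLcr floor, so its single creatinine limit can pass women already below the CLcr at which the protocol says ribavirin should stop

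*Protocol*

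**What the plan says.** Section 4.2, exclusion 8, lists laboratory values that bar entry. The only renal one is "Creatinine > 1.5 mg/dL", the same for men and women. No criterion in Sections 4.1 or 4.2 states a creatinine clearance or GFR. Hemoglobin, in the same list, is split by sex: "Hemoglobin < 12 g/dL for women and < 13 g/dL for men".

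Section 9.5.2 says "The central laboratory will estimate the creatinine clearance" with the MDRD-derived formula, but prints no coefficients. Section 9.5.7.6.4 uses that estimate on treatment: "RBV should be discontinued in subjects with creatinine > 2mg/dL or CL Cr < 50 mL/min". The parent Section 9.5.7.6 describes its contents as guidance: "General guidance is provided in the sections below". Section 6.2 adds a binding consequence: "If RBV is interrupted for more than 14 consecutive days, TMC435 must be discontinued".

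**The concern.** The stopping statement has two arms, joined by "or", and the entry rule mirrors only one. A creatinine of 1.5 mg/dL is comfortably under 2 mg/dL, but the MDRD estimate also depends on sex and age. The same creatinine therefore means a much lower clearance in an older woman than in a young man.

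The other PegIFN/ribavirin laboratory thresholds sit clear of their entry limits:

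| Value | Entry | On-treatment action |
|---|---|---|
| Hemoglobin, no cardiac disease (Table 8) | at least 12 (women) or 13 (men) g/dL | ribavirin reduced < 10, stopped < 8.5 g/dL |
| ANC (Table 9) | at least 1500/mm³ (1000 for black African descent) | PegIFN reduced < 750/mm³ |
| Platelets (Table 10) | at least LLN | PegIFN reduced < 50,000/mm³ |
| Creatinine | at most 1.5 mg/dL | ribavirin stopped > 2 mg/dL |
| CLcr | none | ribavirin stopped < 50 mL/min |

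A subject could be started on ribavirin although the screening creatinine already implies that it should be stopped. Either the guidance is not followed, or ribavirin is withdrawn early and, after more than 14 days, TMC435 goes too. The reason would have been knowable at screening.

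**Working it through.** The protocol gives no figure to reproduce. The check is whether a creatinine that passes exclusion 8 can correspond to CLcr < 50.

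**Inputs from the protocol.** Highest admissible creatinine 1.5 mg/dL (4.2); ribavirin threshold 50 mL/min (9.5.7.6.4); ages 18 to 70 (4.1).

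**Assumed, because the protocol names MDRD but does not print it:**
- 4-variable form: k × Scr^-1.154 × age^-0.203 × 0.742 (female) × 1.212 (black), with k = 186 or 175.
- 6-variable form: 170 × Scr^-0.999 × age^-0.176 × BUN^-0.170 × albumin^0.318 × 0.762 (female) × 1.18 (black), with BUN 15 mg/dL and albumin 4.2 g/dL.

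**Worked case: non-black woman aged 60, creatinine 1.5.**
- k = 186: 186 × 0.6263 × 0.4355 × 0.742 = 37.6.
- k = 175: 37.6 × 175/186 = 35.4.
- 6-variable: 170 × 0.6669 × 0.4865 × 0.6311 × 1.5783 × 0.762 = 41.9.

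**Non-black women, estimate at creatinine 1.5:**

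| Form | 40 | 50 | 60 | 70 |
|---|---|---|---|---|
| k = 186 | 40.9 | 39.1 | 37.6 | 36.5 |
| k = 175 | 38.5 | 36.8 | 35.4 | 34.3 |
| 6-variable | 45.0 | 43.2 | 41.9 | 40.7 |

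With BUN varied from 10 to 20 mg/dL and albumin from 4.0 to 4.5 g/dL, the 6-variable values at these ages stay between 38.2 and 49.2.

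**Creatinine at which the estimate equals 50.** For the 4-variable form this is (k × age^-0.203 × 0.742 / 50)^(1/1.154). At age 60 with k = 186: (186 × 0.4355 × 0.742 / 50)^(1/1.154) = 1.2022^0.8666 = 1.17.

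| Form | 40 | 50 | 60 | 70 |
|---|---|---|---|---|
| k = 186 | 1.26 | 1.21 | 1.17 | 1.14 |
| k = 175 | 1.19 | 1.15 | 1.11 | 1.08 |
| 6-variable | 1.35 | 1.30 | 1.26 | 1.22 |

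The gap is the band from these values up to 1.5 mg/dL. It does not reach every mildly raised creatinine: at 1.2 mg/dL, women of 40 and 50 are still at 52.9 and 50.5 (k = 186) or 56.2 and 54.0 (6-variable).

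**Where the gap narrows or closes.**
- Younger non-black women at 1.5: 45.2 to 48.1 at age 18 and 40.8 to 43.3 at 30 (4-variable); 51.7 and 47.3 (6-variable), so it closes at 18 on that form.
- Black women: crossing point 1.49/1.43/1.39/1.35 at 40/50/60/70 (k = 186); by the 6-variable form 1.59/1.53/1.48/1.44, closed at 40 and 50.
- Non-black men at 1.5: age 60, 50.7 (186) or 47.7 (175); age 70, 49.2 or 46.3; never below 50 by the 6-variable form.
- Black men: never below 50.

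**Units.** MDRD gives mL/min per 1.73 m², whereas the threshold is printed in mL/min. If it were read as unindexed, a woman of 2.0 m² would need an indexed value below 50 × 1.73/2.0 = 43.25. At age 40 the crossing point then moves from 1.26 to 1.43 (k = 186), still inside the gap, and from 1.35 to 1.56 (6-variable), outside it. For a woman smaller than 1.73 m² the shift goes the other way and the gap widens.

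**The case against.** The strongest reply is that exclusion 8 is not the only renal gate. Exclusion 7 bars anyone with a contraindication to ribavirin under local prescribing information, its list is expressly non-exhaustive, and Section 9.1.2 repeats that the local product information bears on eligibility. If that label sets a clearance limit, these women are already out. Section 9.1.2 also says, for out-of-range tests not named in Section 4.2, that "the subject may be included only if the investigator judges the abnormalities or deviations from normal to be not clinically significant" or appropriate for the population; CLcr is not named there, so a reported low value could fall under that rule. Exclusions 9 and 15 give further discretion. This stands in part: some subjects would be caught. But the label is not in the protocol and may differ by country, the other gates rest on history or judgment, and none states the value of 50.

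A second reply is that Section 9.5.7.6.4 is toxicity guidance ("should"), and nothing obliges an entry criterion to match it. That is correct, and this is not a breach of a mandatory stopping rule. It remains the protocol's stated point for stopping ribavirin, and Section 6.2 attaches a mandatory consequence to a prolonged stop.

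Third, the hemoglobin comparison holds only for the Table 8 row "Hemoglobin in subjects with no cardiac disease". With stable cardiac disease, ribavirin stops below 12 g/dL after 4 weeks at reduced dose, and women may enter at 12. That weakens the side comparison but not the renal mismatch.

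Finally, the formula, BUN, albumin and body size are assumptions, and biochemistry is repeated at baseline and Weeks 1, 2, 4, 8 and 12. Monitoring would find a low estimate, but only after ribavirin had been started.

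**Conclusion.** The concern holds. On its numbers alone, exclusion 8 can pass a subject whose MDRD estimate is already below the 50 mL/min at which the protocol says ribavirin should be discontinued. For non-black women aged 40 to 70 this is so at creatinine 1.5 mg/dL on every MDRD form tried (34.3 to 45.0), with the gap opening at about 1.08 to 1.35 mg/dL. It is narrower for black women, touches only older non-black men near the limit, and does not reach black men.

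This rests on standard MDRD coefficients that the protocol does not print and on reading 50 mL/min on the MDRD scale. An unindexed reading closes the gap only for large women of about 40 to 50 on the 6-variable form. How many subjects fall in the band is unknown and probably few.

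The weight is safety and internal consistency. Bias in the primary result should be limited, since subjects who lose ribavirin and TMC435 early would be expected rarely to meet the Week 2, 4 and 8 conditions in Section 3.1 for the 12-week group; the protocol has no data on that point. It should be corrected, but it does not threaten the trial's conclusion.

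**What to change.** Add one line to the laboratory list in exclusion 8: CLcr (MDRD, central laboratory) < 50 mL/min. This uses the protocol's own threshold and an estimate the central laboratory already makes from the biochemistry drawn at screening. If the sponsor's clinicians want room above the stopping value, as there is for hemoglobin and ANC, they can set a higher floor.

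The cost is one line in an amendment and a few screened subjects who become ineligible. No test or visit is added.
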